#### Minimizing treatment bias

A standardized operation technique will be used in both groups. The same LigaSure™ device will be used in the LVSS group. The physician responsible needs to have experience of at least 100 pp-Whipple procedures and will be trained and updated every three months to guarantee comparable treatment of patients.

#### Minimizing measurement bias

A study nurse will document and monitor the procedure in the operating theatre. The patients are blinded for the used operation technique. Physicians' blinding is not possible due to the different techniques used during the operation.

### Study treatment

The surgical technique of PPW procedure is highly standardized in the surgical department and consists of the following operative steps [12,13]: After mobilization of the hepatic flexure of the colon, the duodenum and head of the pancreas are separated from the retroperitoneal bed (Kocher maneuver). The gallbladder is removed and the bile duct is divided above the cystic duct entry across the common hepatic duct. Next, the portal vein is exposed. After division of the right gastric artery, the gastroduodenal artery and gastroepiploic vessels, the duodenum distal to the pylorus is divided. The pancreas is transected in front of the portal vein using a scalpel and not with the Ligasure Impact™ device. Dissection of the distal duodenum proximal to the ligament of Treitz is then performed. This is followed by the reconstruction phase, with preparation and resection of the proximal 10-15 cm section of the jejunum at a point that will provide sufficient mobility of the jejunum to reach the right upper quadrant after it is brought through the transverse mesocolon for the biliary and pancreatic anastomosis. Pancreatojejunostomy is performed with two layers, end-to-side, after mobilization of the pancreatic stump. The end-to-side hepatojejunostomy is made with a single layer and is placed about 10-15 cm aboral of the pancreatojejunostomy. Finally, an end-to-side duodenojejunostomy with two layers is performed about 50 cm distal to the pancreatojejunostomy in an antecolic position.

#### Experimental group

In the LVSS group, dissection and hemostasis of vessels with a diameter of up to seven millimeters (Figure 2) as well as bowel transection (Figure 3) will be performed with the Ligasure Impact™ device (Valleylab™, Boulder, Colorado, USA). For safety reasons, the transected bowel will be overstitched and larger vessels will be ligated in the LVSS group.

**Figure 2 F2:**
[figure not shown]
**Dissection with the LVSS in pylorus-preserving pancreatoduodenectomy**.

**Figure 3 F3:**
[figure not shown]
**Transection of the proximal duodenum with the LVSS**.

#### Control group

In the conventional group, scissors, ligatures, clips and sutures will be used for dissection and hemostasis. Transection of the small bowel will be done with a Linear Cutter 55 2.0 mm (Ethicon Endo-Surgery, Inc., USA).

### Primary and secondary endpoints

#### Primary endpoint

The primary endpoint will be the operating time of the randomized dissection technique.

Definition of the primary endpoint:

The operation time will be measured from the beginning of the surgical procedure (incision of the skin) to the end of the surgical procedure (closure of the skin). It will be documented in the operation log.

Assessment of the primary endpoint:

The operating time will be assessed postoperatively in the case report file (CRF) by the physician responsible and will be confirmed by an independent study nurse. A comparison to the operation report will ensue.

#### Secondary endpoints

• Perioperative complications:

○ Intraoperative Bleeding

○ Perforation of hollow organs (stomach, small intestine, colon, gallbladder/biliary tract)

○ Lesion in parenchymatous abdominal viscus (liver, spleen, pancreas)

• Postoperative complications:

○ Secondary bleeding/hematoma

○ Wound infection

○ Gastroparesis

○ Postoperative pancreatic fistula (POPF)

○ Intraabdominal abscess

○ Anastomotic leakage of the choledochojejunostomy

○ Anastomotic leakage of the gastrojejunostomy

• Re-intervention (operational/interventional)

• Intraoperative blood loss

• Hospital stay

• Re-hospitalization-rate (30 days postoperative)

• Duration of anesthesia

• Intraoperative material consumption

• Material costs, calculated by the material consumption

• Overall costs of the operation, calculated by the indirect and direct costs during the hospital stay and the costs accumulated 30 days postoperatively

• Local recurrence of disease

• Quality of life analysed in questionnaires (EORTC QLQ-C30, EORTC QLQ PAN26, special questionnaire of the European Pancreas Center, University of Heidelberg)

• Mortality rate

Definitions of secondary endpoints are shown in Table 2.

**Table 2 T2:** Definition of secondary endpoints

Perioperative complications	Complication	Definition
Bleeding	Severe intraoperative bleeding	Mentioned in operation report

Perforation of hollow organs	Perforation of stomach, small intestine, colon or biliary tract/gallbladder	Mentioned in operation report

Lesion in parenchymatous abdominal viscus	Lesion in liver, spleen, pancreas	Mentioned in operation report

Postoperative complications	Complication	Definition

Secondary bleeding/hematoma	postoperative bleeding	Need for more than 2 units of red blood cells within 24 hours after surgery OR Need of surgical treatment (mentioned in re-operation report)
	
	Hemtoma	Radiological (ultrasound, CT) findings positive for reoperation or reopening of the wound

wound infection		Deep and/or superficial according to CDC definition [20]

Gastroparesis	delayed gastric emptying (DGE)	Consensus definition of delayed gastric emptying after pancreatic surgery of the International Study Group of Pancreatic Surgery (ISGPS) [21]

pp-Whipple specific complications	postoperative pancreatic fistula (POPF)	Drain output of any measurable volume of fluid on or after postoperative day 3 with an amylase content greater than 3 times the serum amylase activity. Three different grades of POPF (grades A, B, C) are defined according to the clinical impact on the patient's hospital course [22]
	
	Intraabdominal abscess	Intraabdominal collection of purulent or infected fluids (positiv bacterial culture) requiring radiological (puncture or drainage of purulent fluid) or surgical intervention (re-operation)
	
	anastomotic leakage of choledochojejunostomy	Bilirubin-rich (more than 5000 units) drainage fluid of more than 50 ml per day on or after the 10th postoperative day OR Mentioned in re-operation report
	
	anastomotic leakage of gastrojejunostomy	Radiological findings correlating to gastrojejunostomy insufficiency (e.g. CT with contrast medium withdrawal) OR Mentioned in re-operation report

Further secondary endpoints		Definition

Re-intervention	operational	Reoperation due to any cause

	interventional	Interventional haemostasis or drainages due to any cause

Intraoperative blood loss		Mentioned in operation report

Hospital stay		Time of admission to discharge

Re-hospitalization-rate		Re- hospilization within 30 days after surgery due to any cause

Duration of anesthesia		Mentioned in anesthesia report

Intraoperative material consumption		All materials, which are necessary for surgery

Material costs		Costs, which occurs due to the material consumption during the surgery

Overall costs		Costs include expenditure for personnel and use of operating room as well as for material consumption

Local recurrence of disease		Radiological (ultrasound, CT) findings positive for recurrence of disease

Quality of life		EORTC QLQ-C30, EORTC QLQ PAN26 and special questionnaire of the European Pancreas Center Heidelberg on day 30 (±10days), 90 (±10 days), 180 (±10 days), 1 year (± 1 month), 1,5 years (± 1 month), 2 years (± 1 month), 2,5 years (± 1 month) and 3 years (± 1 month)

Mortality rate		Death to any course until year 3 after operation

Assessment:

1. Perioperative complications of the pp-Whipple procedure will be recorded on the day of operation by an independent study nurse.

2. Postoperative complications of the pp-Whipple procedure will be recorded in patients' discharge data and on visit 1 (30 days after operation) after a standardized telephone interview by a study nurse. A confirmation by the patient's family physician will be requested following any abnormality reported by the patient. The following standard aftercare takes place initially twice quarterly (visit 2, 3 months after operation; visit 3, 6 months after operation) then half-yearly for two years (visit 4, 12 months after operation; visit 5, 18 months after operation; visit 6, 24 months after operation; visit 7, 30 months after operation and visit 8, 36 months after operation) with a clinical examination, imaging (ultrasound, CT, MRT), general and standardized questionnaires (EORTC-QLQ-C30, EORTC-QLQ-PAN26 and a special questionnaire from the European Pancreas Center) and laboratory value control in the European Pancreas Center at the surgical department.

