### Eligibility

#### Inclusion criteria

• Clinical suspicion of a cancerous tumour on the head of the pancreas, relied on imaging and laboratory values

• Aged 18 years or older

• Patients scheduled for primary pp-Whipple procedure

• Informed consent

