##### Past medical history

Prior and concomitant illness of the patients will be documented in the CRF. The category of the primary disease (reason for pp-Whipple procedure) is one of the variables to be analyzed for baseline comparability.

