## Analysis

Comparisons will be made of the primary endpoints of both intervention groups for all randomized patients who underwent surgery involving the pp-Whipple procedure. Patients will be analysed as randomized applying the ITT principle [18]. In addition, a per-protocol analysis will be performed, including patients who are strictly treated according to the study protocol.

The outcome measures of the primary endpoint will be tested confirmatory applying an analysis of covariance with treatment as factor and age and BMI as continuous covariates.

Secondary endpoints will be analysed in a descriptive manner. Graphically methods will be used by means of box- and scatter- plots. For all continuous secondary endpoints a t-test will be applied, possible differences of categorical secondary endpoints will be analysed using chi-square tests. All p-values will be used as descriptive statistics only without any confirmatory value.

The secondary endpoint Quality of Life (EORTC QLQ-C30, EORTC QLQ PAN26) will be anlysed by an application of analysis of covariance that adjusts for age and EORTC QLQ-C30, EORTC QLQ PAN26 before surgery.

The following procedure will be applied for missing data:

If at least half of the items from the scale have been answered, the missing items are replaced by the average of those items that are not missing (calculated average rounded to the nearest integer). If less than half of the items from the scale have been answered, the scale is set to missing [19].

If it is evident that missing items or missing scales are related to a worsening in physical functioning, the missing values are replaced by the worst value measured in the respective intervention group at the respective time point.

The average EORTC QLQ-C30, EORTC QLQ PAN26 score can be calculated, if at least one measurement at day 30 (±10days), 90 (±10 days), 180 (±10 days), 1 year (± 1 month), 1,5 years (± 1 month), 2 years (± 1 month), 2,5 years (± 1 month) or 3 years (± 1 month) after surgery is available; if no measurement of the EORTC QLQ-C30 or EORTC QLQ PAN26 after surgery is available, the secondary endpoint is missing and the patient is therefore not included into the analysis.

All statistical analyses will be performed using SAS^® ^software, Version 9.1 (or higher) of the SAS System for Unix (SAS Institute Inc., Cary, NC, USA).

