## Abbreviations

IMBI: Institute for Medical Biometry and Informatics; c-Whipple: classic-Whipple; pp-Whipple: pylorus-preserving-Whipple; LVSS: LigaSure™ Vessel Sealing System; HF: high frequency; SAS: Statistical Analysis Systems; CRF: case report file; RITA: Real Time Interactive Applications; KSC: Clinical Study Venter Surgery; PPW: pylorus-preserving Whipple; POPF: postoperative pancreatic fistula; EORTC: European Organisation for Research and Treatment of Cancer; QLQ-C30: Quality of Life Questionnaire-Core 30; QLQ-PAN26: Quality of Life Questionnaire- Pancreatic Cancer Module 26; CT: computed tomography; MRT: magnetic resonance tomography; AEs: adverse events; SAEs: serious adverse events; ITT: intention to treat; CDC: Centers for Disease Control and Prevention; DGE: delayed gastric emptying; ISGPS: International Study group of Pancreatic Surgery.

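### The Table 2 definition of local recurrence leaves out MRI, which follow-up uses, and names no local site

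*Protocol article*

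**What the plan says.** The list under Secondary endpoints names the endpoint "Local recurrence of disease", and Table 2, which holds the definitions of the secondary endpoints, carries the same label. The definition beside that label is "Radiological (ultrasound, CT) findings positive for recurrence of disease". It lists two modalities and no site.

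The assessment text after Table 2 describes aftercare at visits 2 to 8, from 3 to 36 months after operation, "with a clinical examination, imaging (ultrasound, CT, MRT), general and standardized questionnaires". The Abbreviations section resolves the third modality: "MRT: magnetic resonance tomography". In the study visit schedule (Table 1), the single mark for local recurrence appears to stand in the column for visits 2 to 8, so these are the visits at which the endpoint is ascertained.

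The Analysis section treats secondary endpoints descriptively, with chi-square tests for categorical ones, and gives their p-values no confirmatory role.

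**The concern.** An endpoint definition tells whoever codes the event what counts. This one raises two difficulties.

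First, its modality list is narrower than the imaging that the same article plans for the visits concerned. A coder who follows Table 2 must set aside a positive MRI.

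Second, the word that gives the endpoint its meaning, local, stands in the label but not in the definition. The definition neither names the operative field nor says what to do with distant disease. Two coders could reasonably classify an isolated liver metastasis on CT differently.

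At stake is the one listed endpoint that speaks directly to whether the dissection technique affects tumour control in the operative field. If site and modality are not fixed, coding may vary between patients, and the three-year comparison becomes harder to interpret.

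**Working it through.** The article gives no recurrence figure to reproduce, so the check sets the texts side by side and applies the Table 2 wording to each kind of finding.

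**Inputs**
- Label (Secondary endpoints and Table 2): local recurrence.
- Definition (Table 2): positive ultrasound or CT finding; no site.
- Imaging at visits 2 to 8 (assessment text after Table 2): ultrasound, CT, MRI.

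**Application**

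| Finding at a planned visit | Counted by the definition text | Counted if the label also limits it | Is it a local recurrence? |
|---|---|---|---|
| Local, on ultrasound or CT | yes | yes | yes |
| Local, on MRI only | no | no | yes |
| Distant only, on ultrasound or CT | yes | no | no |
| Distant only, on MRI only | no | no | no |

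Row 2 is wrong under either reading, because the label does not add a modality. Row 3 depends on the reading: the definition text alone counts it, and the label taken as a restriction does not. Rows 1 and 4 are right under both.

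**Effect on the observed rate.** Let L be the true risk of local recurrence in an arm, s the share of local recurrences that ultrasound or CT shows at some point in follow-up, and d the proportion of patients with distant-only recurrence coded as local. Then

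observed rate = s × L + d.

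If s and d are the same in both arms, the observed difference is s × (L1 − L2). Missed MRI-only events shrink the absolute difference by the factor s. The term d cancels from the difference but adds noise and pulls the ratio of the two rates towards 1. With s = 1 and d = 0 nothing is lost. The article gives neither quantity, so s can lie anywhere from 0 to 1, and d anywhere from 0 to the full proportion with distant-only relapse. The two errors act in opposite directions on the rate, but nothing makes them cancel.

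**What limits row 2.** A recurrence first seen on MRI may show on CT or ultrasound at a later visit. It is then counted late rather than lost. The article also does not say which modality is used at which visit, so the frequency of MRI-only findings cannot be derived from it.

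**The case against.** The best defence starts from the table's layout. The left column already says local, and the right column says only how that event is found. On this reading distant disease was never meant to count, and the exact site can sit in the full protocol or the CRF. The modality list does not say only. The same two modalities in parentheses recur in the hematoma row, so they may be habitual wording rather than a deliberate exclusion. Finally, the stated aim is operation time and complication rates, and the article promises no conclusion on local control.

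Much of this stands. The label makes the site question an ambiguity, not a declared rule that distant disease counts, and the intended meaning is probably local. The modality mismatch is not answered in the same way. The parenthesis reads as a closed list, whereas the gastrojejunostomy leakage entry in the same table introduces its imaging as an example. Habitual wording would explain the omission but would still give the coder the wrong instruction. Nor is this detail that an article leaves to another document: the article states the definition, and its own follow-up text does not fit it.

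A reader might go further and infer that patients without cancer dilute the endpoint. Entry rests on "Clinical suspicion of a cancerous tumour on the head of the pancreas, relied on imaging and laboratory values", and under Past medical history "The category of the primary disease (reason for pp-Whipple procedure) is one of the variables to be analyzed for baseline comparability", so some patients with benign histology may be randomized. The documents do not support this as a finding. The population sentence, "for all randomized patients who underwent surgery involving the pp-Whipple procedure", is written for the primary endpoint. No text puts benign cases in the recurrence denominator, and the analysis set for a descriptive secondary endpoint may properly be left to the SAP, which is not shown. A chance imbalance in benign cases between randomized arms would in any case be sampling variation, not bias.

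**Conclusion.** The point holds as a badly fixed definition. Followed as written, it leaves out local recurrences seen only on MRI, although MRI is among the planned imaging. Its text also lacks the local restriction that the label carries, so distant-only recurrence on CT or ultrasound could be coded as local.

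It would be too strong to say that the endpoint does not measure local recurrence, or that it counts every radiological recurrence. Local recurrence on ultrasound or CT is captured, and the label can be read as excluding distant disease.

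No magnitude can be derived, and the number of events affected may be zero. The conclusion assumes that coders apply the Table 2 wording as it stands and that no fuller definition in an unshown document overrides it. Nothing in the article suggests that the choice of modality differs by arm, so no direction of bias is claimed. The primary endpoint and its analysis are untouched, and the consequence is confined to one descriptive secondary endpoint.

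**What to change.** Reword the Table 2 entry along these lines: recurrence in the resection bed or regional lymph nodes on ultrasound, CT or MRI. Record distant-only recurrence as a separate item, so that a patient with an isolated distant finding is not entered as a local event. Use the same modality list in the aftercare text and on the CRF.

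The cost is small: one table row, a site field on the form, and coding by site when imaging reports are read. It needs no additional visit, scan or patient, because MRI is already among the planned follow-up imaging. The change should be made before recurrence data are compared between arms. Any events already coded under the present wording should be reviewed against the new definition by someone unaware of the allocation.

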## Methods/Design

### Aim of study

The comparison of LVSS versus conventional dissection technique in pylorus-preserving pancreatoduodenectomy regarding operation time and complication rates.

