**Examination of primary endpoints**:				
Mortality		X	X	X
Peri- and postoperative complications		X	X	X
Re-intervention			X	X
Intraoperative blood loss		X		
Hospital stay			X	
Reuptake			X	X
Time of anesthesia pre- and postoperative		X		
Intraoperative material consumption		X		
Local recurrence				X
Quality of life	X			X

Safety criteria AE, SAE (2.6)		X	X	X

* study-relevant past medical history, past surgical history

** height (cm), weight (kg), gender, Karnowsky-Index, medication of immunsuppresion, antibiotics, chemotherapy

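### Re-intervention has no time limit and mortality is defined only to year 3, so both endpoints mix early operative events with later disease-related ones and dilute any early difference between techniques

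*Protocol article*

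**What the plan says.** The aim is to compare the two techniques "regarding operation time and complication rates" (Aim of study). The Background section names re-operation and raised morbidity and mortality as possible consequences of poor dissection.

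Table 2 (Secondary endpoints) defines the two outcomes as follows:
- Mortality: "Death to any course until year 3 after operation". No 30-day, 90-day or in-hospital version is defined, and the endpoint list gives only a mortality rate.
- Re-intervention: "Reoperation due to any cause" for the operational part and "Interventional haemostasis or drainages due to any cause" for the interventional part. Neither carries a time limit.

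Table 1 schedules re-intervention at visit 1 (day 30) and at visits 2-8 ("Re-intervention X X"). The assessment text under Secondary endpoints places visit 8 at 36 months. Mortality is ticked for the day of operation, visit 1 and visits 2-8 ("Mortality X X X").

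By contrast, re-hospitalization is limited to 30 days after surgery, and the overall-cost endpoint also runs to 30 days. The Analysis section compares categorical secondary endpoints by chi-square test, with p-values that are descriptive only.

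**The concern.** Re-operation and death are outcomes that the protocol itself links to the quality of dissection. As defined, a drainage for tumour progression at month 20 counts the same as a re-operation for bleeding on day 2. A death from recurrent cancer in year 3 counts the same as a death in the first week. The inclusion criteria require clinical suspicion of cancer, and local recurrence is an endpoint of its own, so later disease-related events must be expected in both arms.

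A test on ever/never by year 3 then has a smaller contrast and more binomial noise than a test on the early period. An early difference between techniques in these two outcomes, in either direction, could be reported as similar rates.

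**Working it through.** **Figures in the document.** The only sample-size calculation concerns operating time (difference 40 min, SD 66 min, two-sided 5%, 80% power). The exact t-test gives 43.7, hence 44 per group, with power 0.803 at 44. That matches the stated 88 patients, and adding 14 gives 102, or 51 per group. No rate, sample size or power is stated for mortality or re-intervention, so there is no figure on this point to reproduce. Everything below uses n = 51 per arm from the document and **assumed** event rates.

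**Dilution.** Let e1 and e2 be the early risks in the two arms, and L the later risk among patients without an early event, taken as equal in both arms.
- Risk by year 3: P = 1 - (1 - e)(1 - L).
- Difference by year 3: P2 - P1 = (e2 - e1)(1 - L).

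The early difference is thus multiplied by (1 - L), whatever the early rates are.

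**Re-intervention, assumed 10% vs 25% early.** z = (P2 - P1) / sqrt{[P1(1 - P1) + P2(1 - P2)] / 51}. For the early reading, 0.15 / sqrt[(0.09 + 0.1875)/51] = 0.15/0.0738 = 2.03.

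| Later risk L | P1 | P2 | Difference | z |
|---|---|---|---|---|
| 0 (early reading) | 0.100 | 0.250 | 0.150 | 2.03 |
| 0.10 | 0.190 | 0.325 | 0.135 | 1.58 |
| 0.20 | 0.280 | 0.400 | 0.120 | 1.29 |
| 0.30 | 0.370 | 0.475 | 0.105 | 1.08 |
| 0.40 | 0.460 | 0.550 | 0.090 | 0.91 |

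**Death, assumed 3% vs 8% early.** The same formula gives z = 1.11 early. With L = 0.30, 0.50 and 0.60 the difference falls from 5 points to 3.5, 2.5 and 2.0 points, and z to 0.37, 0.25 and 0.21.

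**Death with a larger assumed contrast, 3% vs 15%.** Two-sided 5% power by the normal approximation, with pooled variance under the null hypothesis, is 56% for the early reading. With L = 0.30, 0.50, 0.70 and 0.80 the difference falls from 12 points to 8.4, 6.0, 3.6 and 2.4 points, and power to 14%, 9%, 6% and 5%.

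The direction is the same throughout. The size depends entirely on the assumed rates.

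**The case against.** The strongest reply is that little is lost. Deaths are recorded on the day of operation and at day 30, so early mortality can be derived from the planned data, and a separate analysis plan could tabulate it. Intraoperative bleeding, secondary bleeding, pancreatic fistula, abscess, anastomotic leakage and 30-day re-hospitalization are endpoints in their own right. A day-2 re-operation for bleeding already counts under secondary bleeding. All secondary p-values are descriptive. The 10% vs 25% example starts just above the conventional threshold, so any dilution crosses it, and early death at 3% vs 8% would not be detectable in any window.

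Most of this stands, and it limits the point. It does not remove it. Table 2 is where the endpoints are fixed, and it fixes year 3 for death and nothing for re-intervention, while re-hospitalization is given 30 days. This is a stated definition, not a detail left open. Picking an early cut-off after the data are seen is what a defined endpoint should prevent.

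Three stronger readings are tempting and are not supported:
- *That disease events swamp any effect of technique, or make up most of the events.* The documents give no mortality, recurrence or re-intervention rate. Only the direction of the dilution can be shown.
- *That the trial could not see early operative harm.* The separate complication endpoints would still show it.
- *That Table 1 contradicts the assessment text on the complication window.* Table 1 ticks "Peri- and postoperative complications" at visits 2-8 as well, while the text says "Postoperative complications of the pp-Whipple procedure will be recorded in patients' discharge data and on visit 1 (30 days after operation". That paragraph runs on into visits 2-8 with clinical examination and imaging, and it does not say that recording ends at day 30.

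**Conclusion.** The point holds for two descriptive secondary endpoints. As defined, re-intervention and mortality pool early operative events with later disease-related ones, and a simple comparison of proportions shrinks any early difference by the factor (1 - later risk). This rests on a later risk that is equal in both arms and unrelated to the technique. In the assumed re-intervention example the difference falls from 15 points to between 13.5 and 9 points. The true size cannot be derived from the documents. The operating-time analysis and the sample size are untouched. The change is worth making because it costs little and clarifies two outcomes that the protocol ties to dissection. It does not bear on the validity of the main result.

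**What to change.** In Table 2:
- Define re-intervention and operative mortality as events within 30 days of surgery (visit 1), the window already used for re-hospitalization. Assign events by their date.
- Add 90-day figures from visit 2 as supplementary.
- Keep all-cause mortality to year 3 as a separate oncological endpoint.
- List re-interventions after the 30-day window separately as late events.

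The cost is wording in Table 2 and the matching entry in the analysis plan. Visits 1 and 2 already fall at 30 days and 3 months, so no visit is added. The one small drawback is that late device-related re-interventions move to a separate line, where they remain visible.
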